#### Inclusion Criteria

The study will include patients already accepted for fixed orthodontic appliance treatment (“train track”–type braces) at the EDH. Patients at all stages of treatment will be recruited. Patients must also be 10-18 years of age (inclusive), be familiar with and have daily access to a smartphone or tablet, and be able to read and communicate in English, as the app is currently available only in English.

#### Exclusion Criteria

Patients with severe hypodontia (developmental absence of teeth) and craniofacial/orthognathic patients will be excluded from this study. These patients require complex multidisciplinary treatment; the information needs for these patients are therefore different. Treatment involves input from specialties other than orthodontics, and this may therefore influence adherence to treatment advice.

Patients with communication difficulties (for example, severe autism or learning difficulties) will also be excluded from the study.

#### Recruitment

A convenience sample will be recruited for phase 1. Patients meeting the inclusion criteria and willing to participate in the feasibility study will be enrolled. Patients at different stages of treatment will be recruited as follows: 20 patients who have been accepted for fixed orthodontic appliance treatment but who have not yet started treatment, 20 patients who are currently in fixed appliance treatment, and 20 patients who have completed treatment and are wearing retainers.

The reason for allocating patients in this manner is that the app is designed to support the whole treatment journey (before, during, and after active treatment). Recruiting patients at different stages of this journey therefore ensures that all relevant components of the app are experienced and assessed by an appropriate patient group.

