#### Data Collection

The app will be assessed by current orthodontic patients and tested for quality using the user version of the Mobile Application Rating Scale (uMARS) [17]. The uMARS is a reliable tool for assessing app quality and consists of sections relating to app engagement, functionality, aesthetics, and information [15]. The uMARS quality score can range from 1 (“Inadequate”) to 5 (“Excellent”). Additionally, there is a free text section for patients to provide comments.

It is estimated that the total duration of this phase for each participant will be around 8-12 weeks. Patients will be provided with access to the app and asked to complete the uMARS questionnaire prior to, or at, the next appointment. Patients will be prompted by the My Braces app to complete the uMARS form online using UCL Opinio. After this point, no further data will be collected.

The following baseline details will also be obtained: age, gender, and stage of treatment.

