#### Planned Analyses

The Kruskal-Wallis test will be used to compare the uMARS scores across the three groups and the scores across different sections of the uMARS form.

Any changes felt to be appropriate based on feedback from the uMARS questionnaire will be implemented in the app prior to using it in phase 2.

### Phase 2

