#### Inclusion Criteria

The study will include patients who have been accepted for fixed orthodontic appliance treatment (“train track”–type braces) at the UCLH NHS Foundation Trust EDH but who have not yet commenced treatment. Patients must also be 10-18 years of age (inclusive) at the start of treatment, have a sufficient number of permanent teeth erupted to allow outcome assessment, be familiar with and have daily access to a smartphone or tablet, and be able to read and communicate in English.

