#### Exclusion Criteria

Patients with severe hypodontia (developmental absence of teeth) and craniofacial/orthognathic patients will be excluded from this study. These patients require complex multidisciplinary treatment; the information needs for these patients are therefore different, and treatment involves input from specialties other than orthodontics, and this may therefore influence adherence to treatment advice.

Patients with communication difficulties (for example, severe autism or learning difficulties) will also be excluded from the study.

Patients who are aware that a family member or friend is enrolled in the study (phase 1 or phase 2) will be excluded from the study because it is possible that these patients may become aware of details of the app that may not be relevant to the group that they are randomized to.

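### Phase 2 does not exclude phase 1 participants, so patients still untreated when it opens could enter arms A or B having already used the app

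*Protocol article*

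**What the plan says.** Under Phase 1, Recruitment, one of three groups of 20 is "20 patients who have been accepted for fixed orthodontic appliance treatment but who have not yet started treatment". Under Phase 1, Data Collection, "Patients will be provided with access to the app and asked to complete the uMARS questionnaire prior to, or at, the next appointment", and "It is estimated that the total duration of this phase for each participant will be around 8-12 weeks". Phase 1, Planned Analyses, says that changes suggested by the feedback "will be implemented in the app prior to using it in phase 2", so phase 1 comes first.

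Phase 2, Inclusion Criteria, asks for patients accepted for fixed appliances at the same hospital "but who have not yet commenced treatment". The age, device and language requirements match those of phase 1. The one added requirement is enough erupted permanent teeth for outcome assessment.

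Phase 2, Exclusion Criteria, lists severe hypodontia, craniofacial and orthognathic patients, communication difficulties, and one contamination rule: "Patients who are aware that a family member or friend is enrolled in the study (phase 1 or phase 2) will be excluded". The stated reason is that such patients might learn about app features that do not belong to their own arm. No criterion mentions having taken part in phase 1.

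**The concern.** The contamination rule names phase 1, yet it reaches only people who might hear about the app from a participant. It does not reach people who have used the app, although their exposure is more direct. By the protocol's own reasoning this is a gap.

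The arms differ only in app content. Arm A has the timer, arm B adds generic information, and arm C adds personal data entry, goals, plans and dashboards. A patient in A or B who has already used features reserved for a higher version carries part of the contrast into the comparator. That would tend to shrink C versus A. It would also tend to shrink C versus B, which the protocol includes to isolate personalisation. Prior exposure cannot be undone after randomisation.

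**Working it through.** **1. Eligibility side by side (protocol article, Phase 1 and Phase 2 criteria)**

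| Criterion | Phase 1, pre-treatment group | Phase 2 |
|---|---|---|
| Site | Eastman Dental Hospital | same |
| Treatment status | accepted, not started | accepted, not started |
| Age | 10–18 | 10–18 at start of treatment |
| Device and English | required | required |
| Enough erupted permanent teeth | not required | required |
| Hypodontia, craniofacial/orthognathic, communication difficulties | excluded | excluded |
| Knows a participant | no rule | excluded |
| Took part in phase 1 | not applicable | no rule |

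A phase 1 pre-treatment patient can therefore qualify for phase 2 on two conditions: treatment has not begun by then, and enough permanent teeth have erupted. The eligibility gap follows from this comparison alone. The arithmetic below only sizes it.

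**2. The plan's own sample size (Sample Size section)**

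Inputs: bleeding difference 15, SD 20 (standardised difference 0.75); brushing 0.85; 80% power; alpha 0.05 with an allowance for multiple testing. The method of adjustment and the sidedness are not stated. I assume two-sided 0.05/3, for three pairwise tests.

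n per arm = 2 (z₁₋α/₂ + z₀.₈₀)² / d²

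- Bleeding: 2 (2.394 + 0.842)² / 0.75² = 37.2, rounded up to 38.
- Brushing: 2 (2.394 + 0.842)² / 0.85² = 28.98, rounded up to 29.
- Unadjusted alpha 0.05 would give 28 and 22, so the 0.05/3 assumption fits the plan's figures.
- 38 × 1.2 = 45.6, rounded up to 46 per arm; 46 × 3 = 138.

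The stated 29, 38, 46 and 138 all reproduce.

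**3. How many could be exposed**

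Let k be the number of phase 1 pre-treatment patients who enter phase 2. The documents do not give k; its range is 0 to 20. The upper bound is 20/138 = 14.5% of the trial. With even allocation, 20 × 2/3 ≈ 13 of them would be in A or B.

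**4. Dilution of C versus A on bleeding**

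Assumptions: exposed patients spread evenly over the arms; each one in A keeps a fraction c of the 15-point effect; exposed patients in C respond like the rest of C.

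Difference = 15 × (1 − c × k/138)

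Power is for a two-sample t test (noncentral t), 38 per arm, SD 20, alpha 0.05/3.

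| k | c | Difference | Power |
|---|---|---|---|
| 0 | – | 15.0 | 79.1% |
| 3 | 0.5 | 14.8 | 78.1% |
| 5 | 0.5 | 14.7 | 77.4% |
| 10 | 0.5 | 14.5 | 75.7% |
| 20 | 1 | 12.8 | 63.6% |

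Last row: 15 × (1 − 20/138) = 12.83. The normal approximation gives 80.9% and 65.6% for the first and last rows. The loss in the extreme case is about 15 percentage points by either method.

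**The case against.** **The article is condensed.** A bar on prior participation may stand in the full protocol, and the team may simply have taken it for granted. Nothing in the article says that phase 1 participants may enter phase 2. This makes an oversight in wording the likelier explanation, but it does not remove the point. The article prints both sets of criteria and a contamination rule that names phase 1, and that rule as written admits the most direct source of contamination.

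**Few may qualify.** Phase 2 opens only after phase 1 has been completed and analysed and any app changes made. The pre-treatment patients are already accepted for braces, so some will have started treatment by then, and some may lack enough erupted teeth. This stands: 20 is a ceiling, and zero is possible.

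**Exposure could be read too strongly.** A reader might infer that these patients used the full app for 8 to 12 weeks and so had everything that defines arm C. The documents do not say so. The 8 to 12 weeks is an estimated phase duration per participant, not time in use. The version supplied in phase 1 is not named. The remark that recruitment by stage "ensures that all relevant components of the app are experienced and assessed by an appropriate patient group" describes coverage across the three groups together, not what each patient sees. Full functionality is an inference.

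**The largest power loss is a joint worst case.** It needs all 20 to re-enrol and the whole effect to persist from use before braces were fitted, after A and B patients move to restricted versions. No passage supports such persistence. Prior use could also alter arm C and the baseline scores, which the formula ignores. These points stand, and they limit the claim about size and certainty of direction.

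**Conclusion.** The gap in the phase 2 exclusion criteria is real and can be read directly from the text: following the printed rules, a former phase 1 app user who is still untreated and has enough erupted teeth can be randomised to A or B. Confidence is high on that point and lower on the consequence.

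The likely direction is dilution of C versus A and C versus B. The size runs from nothing, if none re-enrol, through power of about 76% to 78% with 3 to 10 re-enrolled at half carry-over, to 64% in the upper-bound scenario, against about 79% without contamination. These figures rest on an assumed number, even spread, assumed carry-over and alpha of 0.05/3. They show a range and are not a prediction.

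It would go too far to conclude that arms A and B will contain exposed patients, or that the trial is underpowered for this reason. The point is a cheap improvement.

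**What to change.** Add one sentence to the Phase 2 Exclusion Criteria: *Patients who took part in phase 1 are not eligible for phase 2.* It should be in place before the first phase 2 randomisation. If the full protocol already contains such a rule, it is enough to state it alongside the family-and-friends rule.

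The sentence need not extend to the volunteers in the examiner calibration exercises, because nothing in the article says that they receive the app.

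The cost is the loss of at most 20 potential recruits from the pool during a recruitment period of about 18 months. The planned sample size stays at 138, and no analysis changes.

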#### Data Collection

The app will be assessed by current orthodontic patients and tested for quality using the user version of the Mobile Application Rating Scale (uMARS) [17]. The uMARS is a reliable tool for assessing app quality and consists of sections relating to app engagement, functionality, aesthetics, and information [15]. The uMARS quality score can range from 1 (“Inadequate”) to 5 (“Excellent”). Additionally, there is a free text section for patients to provide comments.

It is estimated that the total duration of this phase for each participant will be around 8-12 weeks. Patients will be provided with access to the app and asked to complete the uMARS questionnaire prior to, or at, the next appointment. Patients will be prompted by the My Braces app to complete the uMARS form online using UCL Opinio. After this point, no further data will be collected.

The following baseline details will also be obtained: age, gender, and stage of treatment.

#### Planned Analyses

The Kruskal-Wallis test will be used to compare the uMARS scores across the three groups and the scores across different sections of the uMARS form.

Any changes felt to be appropriate based on feedback from the uMARS questionnaire will be implemented in the app prior to using it in phase 2.

### Phase 2

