#### Planned Analyses

Proposed outcome analyses are summarized in Table 2.

For each of the main outcome measures, it is anticipated that regression analysis will be undertaken. The main factor of interest (group allocation) and confounding variables (eg, age, gender, ethnicity) will be entered into univariable regression analyses to determine the level of significance and to limit the number of variables entered into the multivariable analysis. Any factors with *P*≤.10 will be considered for inclusion in the multivariable analysis. Factors with *P*<.05 in the multivariable analysis will be considered as having a significant effect on toothbrushing time or gingival bleeding. Secondary outcomes will be explored in a similar manner.

If necessary, an intention to treat analysis will be performed; all enrolled and randomized patients will be included in the analysis and analyzed in the groups to which they were randomized.

**Table 2 table2:** A summary of proposed statistics for outcome analysis.

Outcomes	Method of analysis
Toothbrushing duration	Comparison of the 3 groups using an ANOVA, followed by 2-sample *t* tests (A vs B, B vs C, and A vs C) if any statistical significance is found
Bleeding score	Chi-square test
Plaque scores	Comparison of the 3 groups using an ANOVA, followed by 2-sample *t* tests (A vs B, B vs C, and A vs C) if any statistical significance is found
Number of breakages	Kruskal-Wallis test, followed by Mann-Whitney test (A vs B, B vs C, and A vs C) if any statistical significance is found
Number of missed appointments	Kruskal-Wallis test, followed by Mann-Whitney test (A vs B, B vs C, and A vs C) if any statistical significance is found
Total number of appointments	Kruskal-Wallis test, followed by Mann-Whitney test (A vs B, B vs C, and A vs C) if any statistical significance is found
Treatment duration	Comparison of the 3 groups using an ANOVA, followed by 2-sample *t* tests (A vs B, B vs C, and A vs C) if any statistical significance is found
Enamel demineralization	Chi-square test
App subjective quality	Comparison of the 3 groups and different section of the uMARS form by using the Kruskal-Wallis test.
App engagement	Comparison of the 3 groups using an ANOVA, followed by 2-sample *t* tests (A vs B, B vs C, and A vs C) if any statistical significance is found

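### Kruskal-Wallis is planned for comparing uMARS sections that the same patients rate; a matched test is needed (minor, secondary analysis)

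*Protocol article*

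**What the plan says.** The phase 1 Planned Analyses section of the protocol article assigns one test, Kruskal-Wallis, to two contrasts. The first is between the three patient groups. The second, listed separately, is of "the scores across different sections of the uMARS form".

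The three groups are separate patients. The phase 1 Recruitment section sets 20 for each of three stages: before treatment, during it ("20 patients who are currently in fixed appliance treatment") and in retention, which makes 60 in all.

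The sections are not separate patients. The phase 1 Data Collection section says that the uMARS "consists of sections relating to app engagement, functionality, aesthetics, and information", and that patients are "asked to complete the uMARS questionnaire prior to, or at, the next appointment". One completed form therefore gives four section scores from one person.

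For phase 2, the Table 2 row on subjective app quality reads "Comparison of the 3 groups and different section of the uMARS form by using the Kruskal-Wallis test". The phase 2 Data Collection and Other Outcomes sections limit that outcome to sections E and F of the form.

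Neither place names a matched or repeated-measures test. The article gives no expected difference between sections, no correlation between them and no power for this comparison.

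**The concern.** Kruskal-Wallis is valid for the three groups, since no patient belongs to two of them. For the sections, all four samples come from the same 60 people. A patient who likes the app tends to score every section high, and one who dislikes it tends to score every section low. Kruskal-Wallis leaves that patient-to-patient variation in its yardstick, although it cancels when sections are compared within a patient. The reference distribution is then wrong. With positive correlation the p-values are too large.

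The stake is modest but real. The app may be amended after phase 1 in the light of the uMARS feedback, and the section comparison is the only formal analysis that could point to one part being rated below the others. If its true error rate is far below the nominal level, a non-significant result says little. The protocol names this test for this contrast, so the point concerns a stated choice and not a detail left to a fuller document.

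**Working it through.** **Inputs from the protocol article.** 3 × 20 = 60 patients (phase 1 Recruitment); 4 sections and a score range of 1 to 5 (phase 1 Data Collection). The 5% level is stated only in the phase 2 Sample Size section and is assumed here for phase 1.

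**Inputs assumed, because the article gives none.** Within-patient correlation between sections ρ = 0.3, 0.5 or 0.7; shift between sections of 0.4 or 0.6 SD; roughly normal scores rounded to quarter points.

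The plan states no figure for this comparison, so there is none to reproduce first.

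**Step 1. Direction of the error, by formula.** With n patients and section SD σ, the difference between two section means has variance 2σ²(1 − ρ)/n. Kruskal-Wallis works as if it were 2σ²/n. With no true difference its statistic therefore behaves approximately like (1 − ρ) times a chi-square on 4 − 1 = 3 degrees of freedom, and the real error rate is P(χ²₃ > 7.815/(1 − ρ)):

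- ρ = 0.3: 7.815/0.7 = 11.16, giving about 1.1%
- ρ = 0.5: 7.815/0.5 = 15.63, giving about 0.14%
- ρ = 0.7: 7.815/0.3 = 26.05, giving about 0.001%

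**Step 2. Size, by simulation (60 patients, 4 sections, one section lower than the other three).**

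| Setting | Test | ρ = 0.3 | ρ = 0.5 | ρ = 0.7 |
|---|---|---|---|---|
| No difference | Kruskal-Wallis | 1.5% | 0.3% | <0.1% |
| 0.4 SD lower | Kruskal-Wallis | 55% | 49% | 44% |
| 0.4 SD lower | Friedman | 66% | 81% | 96% |

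Friedman's null rejection rate stays close to 5%. Repeat runs of the power figures agree within about 3 points. The null rates match step 1 to within simulation error and the approximation. The relative loss of power at 0.4 SD is 1 − 55/66 = 17%, 1 − 49/81 = 40% and 1 − 44/96 = 54%.

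At a 0.6 SD shift, power is 93 to 98% for Kruskal-Wallis and 96 to 100% for Friedman.

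**Step 3. Does the pattern of means matter?** With four evenly spaced section means and 0.4 SD between highest and lowest, Kruskal-Wallis against Friedman is 38 against 52%, 31 against 68% and 24 against 89% at the same three correlations. With 0.6 SD between them it is 82 against 88%, 84 against 97% and 86 against 100%. At ρ = 0 Kruskal-Wallis loses nothing. The direction is the same under both patterns; the size depends on the assumptions.

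**Step 4. Phase 2.** Only two sections, E and F, are collected, so the four-section figures do not carry over. With two conditions the Friedman test reduces to a sign test. For 138 patients and an assumed shift of 0.3 SD, power for Kruskal-Wallis, Friedman and the signed-rank test is 70, 71 and 83% at ρ = 0.3, and 73, 84 and 93% at ρ = 0.5. The signed-rank test is the better matched choice there.

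**The case against.** A reader might infer that the planned test loses most of its sensitivity, or cannot see a weak section. The article does not support that, because it gives neither the correlation nor the expected difference. With one section 0.4 SD lower, more than half the power is lost only at the highest correlation tried; with evenly spread means it happens from about 0.5 upwards. At a correlation of 0.3 the loss is moderate, and a clearly weak section is found by either test.

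A reader might also infer that a weak section would go unamended. That does not follow. The stated aim of phase 1 is to judge whether end users find the app to be of high quality. Amendments rest on judgement over all the questionnaire feedback, which includes a free-text section, and no rule ties them to a significant result. A low mean on a 1 to 5 scale is visible without a test.

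The error is also conservative: under positive correlation it does not produce excess false positives. And the Table 2 entry is terse enough to mean a comparison of the three randomised groups on each section, for which Kruskal-Wallis is right.

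All of this stands, and it limits the consequence. It does not rescue the phase 1 sentence, which lists the section comparison as a second contrast alongside the group comparison and assigns it an independent-samples test.

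**Conclusion.** The phase 1 plan is wrong as written on this point: an independent-samples test is fixed for within-patient data. The effect is a conservative test that can lose sensitivity to moderate differences between sections, by roughly 11 to 52 percentage points at a 0.4 SD shift in one section (66 − 55 to 96 − 44) over correlations of 0.3 to 0.7, and by little at 0.6 SD. Those sizes rest on the assumed correlation, shift and score distribution; the failure of independence does not. For Table 2 the point is conditional: it applies only if sections E and F are compared with each other. This is a minor correction to a secondary analysis and touches neither primary outcome.

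**What to change.** In the phase 1 Planned Analyses section, keep Kruskal-Wallis for the three independent patient groups. For the comparison between sections, name the Friedman test with paired Wilcoxon signed-rank follow-up.

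In the Table 2 row on subjective app quality, keep Kruskal-Wallis for the three randomised groups and state whether sections E and F are to be compared with each other. If they are, name a paired Wilcoxon signed-rank test.

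Reporting each section's score with a 95% confidence interval would also help, since decisions on the app draw on the scores themselves.

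The cost is a change of wording in two places, with the same data, visits and software. The article reports that no patients had been recruited, so at that point the change could be made before any data were seen.
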